**Methods:**

A total of 132 FSWs will be recruited and randomly assigned to either the intervention or usual care (control) groups in a multi-centred randomised controlled trial. Based on the resilience framework, this intervention is comprised of six weekly sessions focused on the awareness, expression and management of emotions, identifying roles and personal strengths, and effective problem-solving skills. Complex intervention assessment on both intervention process and effectiveness will be adopted when the primary outcome reduction of sexual risk behaviour and other psychological outcomes include their perceived stress, self-esteem, self-efficacy, coping overall resilience, and psychological distress will be measured at baseline, post-treatment and 3-month post-intervention and differences assessed by ANOVA. The relationship of resilience factors, psychological health and HIV preventive behaviours will be evaluated using structural equation modelling.

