### Sample size

Sample size estimation is based on the “always” use condom rate during commercial transactions in the last month at 49.3% from the latest local study published on the topic [16] and an assumption of effect size of 25% on condom use rate between the intervention and control groups from a previous study [43]. In order to detect such a difference with a power of 80% and a two-tailed significance of 0.05, the sample size required is 66 in each group.

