### Effectiveness assessment - primary outcome measures

#### HIV preventive behaviour

Self-reported rate of always using a condom during vaginal sexual intercourse with clients in the previous month and at the last encounter will be used as proxy measures of safe sex behaviour and HIV prevention.

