### Data analyses

First of all, the baseline demographics of the intervention and control groups will be compared with independent sample *t*-tests for continuous variables and *chi*-square for categorical variables to assess the compatibility of the two-trial arms at baseline to ensure both groups were similar to start with. The change of scores on sexual health risks and psychological outcome measures (self-esteem, self-efficacy, coping, resilience and GHQ) over time between two groups will be analysed using analysis of variance with intention-to-treat analysis. Bivariate correlation analyses will be performed to examine the relationship between psychological variables and behavioural outcomes. Linear regressions will also be used to examine the associations and the effects of resilience, self-esteem, self-efficacy, coping on psychological health outcomes and HIV preventive behaviours. The statistical analyses will use SPSS 20.0 and *p*-values of 0.05 or less will be considered statistically significant.

The second objective of the current study is to explore the mechanism of how individual resilience factors influence the psychological outcomes and HIV preventive behaviours in FSWs (as proposed in Figure 1). Structural equation modelling (SEM) identifies connection strengths that best predict the observed structure of the data with respect to the specified model. Thus, SEM will be performed to evaluate the model fit of the proposed model that links psychological resources with harm-reduction behaviours as measured by condom use.

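### The yes/no primary outcome is sized as two proportions but analysed by an unspecified ANOVA of change, which falls short of the stated 80% power if condom use is only weakly correlated within women

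*Protocol article*

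**What the plan says.** The primary outcome, under HIV preventive behaviour, is "Self-reported rate of always using a condom during vaginal sexual intercourse with clients in the previous month and at the last encounter". For each woman both measures are yes or no.

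The Sample size section starts from an always "use condom rate during commercial transactions in the last month at 49.3" per cent, adds "an assumption of effect size of 25% on condom use rate between the intervention and control groups", and works "with a power of 80% and a two-tailed significance of 0.05". It concludes that "the sample size required is 66 in each group". These are the ingredients of a comparison of two proportions.

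The Data analyses section handles "The change of scores on sexual health risks and psychological outcome measures" together, over time and between the two groups, by analysis of variance on an intention-to-treat basis. The Abstract agrees: the sentence that names the primary outcome says the outcomes are "measured at baseline, post-treatment and 3-month post-intervention and differences assessed by ANOVA". Chi-square is mentioned only for baseline comparability. No between-arm method for a yes/no outcome at follow-up is named, nor is one follow-up visit or one contrast singled out.

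**The concern.** The power calculation belongs to one analysis and the plan commits to another. Subtracting a 0/1 baseline from a 0/1 follow-up gives a score of -1, 0 or 1 that carries the full baseline variance. Unless a woman's condom use at baseline predicts her later use fairly well, this adds more noise than it removes. A repeated-measures ANOVA over three visits adds a second issue: its group-by-time test has 2 degrees of freedom and does not isolate the single between-arm difference that the trial was sized to detect.

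At stake is whether 66 per arm gives the stated 80% power for the primary comparison. The baseline value is collected in any case and could be used in a way that gains power instead of risking it.

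**Working it through.** **Inputs from the document.** Control rate p1 = 0.493; difference 0.25, so p2 = 0.743; two-sided alpha 0.05; power 80%; n = 66 per arm; 1:1 allocation. **Assumed, because not given:** the correlation rho between baseline and follow-up always-use, taken as equal in both arms; baseline rate 49.3% in both arms; no loss to follow-up.

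**Step 1: reproduce 66.** The mean rate is (0.493 + 0.743)/2 = 0.618. The usual two-proportion formula gives

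n = [1.960·√(2 × 0.618 × 0.382) + 0.8416·√(0.493 × 0.507 + 0.743 × 0.257)]² / 0.25² = (1.3468 + 0.5588)² / 0.0625 = 58.1, so 59.

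With continuity correction: (58.1/4)·[1 + √(1 + 4/(58.1 × 0.25))]² = 65.9, so 66. This matches. A relative 25% (61.6%) would need 255 per arm, or 271 with correction, so the 25% must be percentage points. (59/0.90 also rounds up to 66, but no dropout rate is stated.)

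**Step 2: variances.** Baseline and control follow-up: vb = 0.493 × 0.507 = 0.2500. Intervention follow-up: vf = 0.743 × 0.257 = 0.1910. √(vb·vf) = 0.2185.

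**Step 3: variance of each contrast, summed over arms and before division by n.**

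- Change at one visit: [2vb − 2·rho·vb] + [vb + vf − 2·rho·√(vb·vf)] = 0.9408 − 0.9368·rho.
- Baseline-adjusted at one visit: (vb + vf)(1 − rho²) = 0.4409·(1 − rho²).

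Power = Φ(0.25/√(V/66) − 1.960).

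| rho | V, change | Power, change | n per arm for 80% with change | V, adjusted | Power, adjusted | Ratio of V |
|---|---|---|---|---|---|---|
| 0 | 0.941 | 55% | 119 | 0.441 | 86% | 2.13 |
| 0.2 | 0.753 | 65% | 95 | 0.423 | 88% | 1.78 |
| 0.3 | 0.660 | 71% | 83 | 0.401 | 89% | 1.64 |
| 0.4 | 0.566 | 77% | 72 | 0.370 | 92% | 1.53 |
| 0.5 | 0.472 | 84% | 60 | 0.331 | 94% | 1.43 |

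With rates moving from 49.3% to 74.3%, rho in the intervention arm cannot exceed about 0.58. At 0.57 the change-score power is 89%. Simulation of paired 0/1 data (40,000 trials per value) agreed with the change-score column to within about one point.

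**Step 4: where change scores reach 80%.** Required V = 66 × 0.0625/(1.960 + 0.8416)² = 0.5256. Setting 0.9408 − 0.9368·rho = 0.5256 gives rho = 0.44. If the contrast is the mean of both follow-ups minus baseline, with the same rho between all visits, V = 1.5·vb·(1 − rho) + vb + vf(1 + rho)/2 − 2·rho·√(vb·vf), which meets 0.5256 at about rho = 0.27.

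**Step 5: the three-visit group-by-time test.** Simulated with the 25-point difference at both follow-ups, its power is about 66%, 75% and 85% at correlations of about 0.2, 0.33 and 0.5.

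**Step 6: validity and scale.** Simulated type I error of the change-score ANOVA was 4.5% to 5.1%. The expected difference in mean change is (74.3 − 49.3) − (49.3 − 49.3) = 25 points, which is the planned risk difference.

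**The case against.** Several objections have force.

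The shortfall depends on a correlation that the document does not give. At 0.5 every version of the ANOVA examined exceeds 80%. A reader might infer that the planned analysis is simply less powerful than the sizing; the figures do not support that without the condition on rho. This stands.

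The text does not say which ANOVA is meant. The averaged-follow-up contrast is also an ANOVA of change, and its simulated power is about 75%, 83% and 90% at correlations of about 0.19, 0.33 and 0.49. This stands too, and is the reason for giving two thresholds. It also shows that the achieved power cannot be stated until the contrast is fixed.

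A reader might infer that ANOVA of a 0/1 change score is invalid, or gives no effect on the planned scale. Neither holds: type I error is kept, and the mean-change difference is a risk difference.

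Part of the advantage of the adjusted analysis comes from the continuity correction in the 66, since 59 suffice without it. That is fair as regards the 80% benchmark. It does not affect the ranking: in this calculation the adjusted contrast has the smaller variance at every correlation examined.

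Finally, an article may leave analytic detail to a fuller document. But the method is not omitted here. ANOVA of change is stated, in both the Data analyses section and the Abstract.

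The Data analyses section also says "Linear regressions will also be used to examine the associations and the effects of resilience" and other factors on outcomes that include HIV preventive behaviours. Those models explore associations and are not the randomised comparison. No harm has been shown, so this is minor.

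**Conclusion.** The mismatch is real and stated in the text: the sizing is for two proportions, the analysis is ANOVA of change, and no visit or contrast is fixed. For assumed correlations of 0 to 0.4, a single-visit change analysis has about 55% to 77% power against the stated 80%. It reaches 80% from about 0.44, or about 0.27 if the two follow-ups are averaged. A baseline-adjusted comparison at one follow-up has about 86% to 94% for correlations of 0 to 0.5.

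These figures assume 49.3% against 74.3%, complete follow-up and a common correlation in both arms. The Sample size section states no dropout allowance, and the Limitations section foresees some drop-out, so realised power would be lower for every method.

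This is a matter of efficiency and consistency with the sizing, not of bias or false-positive control. It should be fixed, because it concerns the primary comparison and the remedy is free, but it does not invalidate the trial.

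**What to change.** In the Data analyses section, and to match in the Abstract, state that always-use in the previous month (yes/no) at one named follow-up will be compared between arms with a binary-outcome model adjusted for baseline always-use. Logistic regression with a marginal risk difference, or modified Poisson regression, would serve. The risk difference should be reported with its 95% confidence interval; a risk ratio can accompany it. The investigators should name the follow-up before outcome data are seen.

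Adjusting the psychological scales for baseline instead of analysing their change is an optional improvement, also free. Using logistic regression where condom use is the dependent variable in the association models is a minor tidying.

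The cost is analysis wording only. Baseline always-use is already collected, and no additional participants, visits or measurements are needed.

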### Participants

FSWs who fulfil the inclusion criteria will be invited and have the study explained to them by the trained outreach staff of the NGOs. Inclusion criteria for the proposed study are: (i) 18 years or older; (ii) acknowledged to have been living and working as a FSW in Hong Kong within the preceding 6 months; and (iii) able to give an informed consent. All potential participants will be screened over the telephone by one of the researchers who is a clinical psychologist to confirm their fulfilment of inclusion criteria and exclude them if they are (i) unable to speak Cantonese/ Putonghua; and (ii) diagnosed with and currently on medical or psychological treatment for a serious psychological health problems such as psychosis, current substance abuse, bipolar disorder, severe affective disorders or have suicidal ideation.

Eligible participants will be provided with further details of the study and those who provide verbal consent will complete the self-reported baseline questionnaire face-to-face. Participants will be randomly allocated on a 1:1 ratio into one of the two groups according to a block randomisation list which was computer-generated. Participants are informed that they would have an equal chance of allocating into any of the two groups and the allocation outcome is unknown to participants until baseline assessment session. The women recruited will be advised not to disclose the content and activities of the intervention to others to avoid contamination. An independent researcher will conduct the baseline, post-intervention, and follow-up assessments and enter the data obtained from the questionnaires.

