#### Risk and sexual risk behaviours

Other information on risk behaviours collected includes sexual acts, number of partners, other risk behaviours such as smoking, drug /alcohol use and dependence, health seeking behaviour, and HIV/ STI testing will also be elicited in the questionnaire.

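### ANOVA of change is the only between-arm method stated for sexual-risk outcomes; for the secondary counts of acts and partners a baseline-adjusted comparison would be more efficient if those counts are skewed (minor)

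*Protocol article*

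**What the plan says.** In the protocol article, the section on risk and sexual risk behaviours falls under the secondary outcome measures. It states: "Other information on risk behaviours collected includes sexual acts, number of partners", followed by smoking, substance use, health seeking and testing. These are measured at baseline, at the end of the intervention and three months later (Study design).

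Data analyses names one between-arm method for outcomes of this kind. "The change of scores on sexual health risks and psychological outcome measures" over time between the two groups "will be analysed using analysis of variance with intention-to-treat analysis". The psychological scales are itemised in brackets; the sexual health risks are not. No baseline covariate, transformation, count model or rank method is mentioned. The abstract also says that differences will be assessed by ANOVA.

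The sample size rests on something else, the proportion of women who always use condoms: an "assumption of effect size of 25% on condom use rate between the intervention and control groups", with "power of 80% and a two-tailed significance of 0.05", so that "the sample size required is 66 in each group".

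**The concern.** Acts and partner numbers are non-negative counts with no fixed ceiling. The Setting section describes recruitment from street work, nightclubs and karaoke bars, one-woman premises, saunas and massage parlours, so wide variation between women would be no surprise. An analysis of variance of change has two weaknesses for such data:

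- It forces a slope of one on the baseline value, which adds baseline noise to the comparison when the two visits are only moderately correlated.
- On the count scale, the error variance is driven by the women with the largest counts.

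Both cost power. Besides the condom-use rates, these counts are the trial's quantitative information on sexual exposure, and a null result from an inefficient test could be over-read.

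**Working it through.** **The plan's own figure.** Inputs from Sample size: 49.3% against 49.3 + 25 = 74.3%, 80% power, two-sided 0.05, allocation 1:1.

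- Mean proportion: (0.493 + 0.743)/2 = 0.618.
- Uncorrected n = [1.96√(2 × 0.618 × 0.382) + 0.8416√(0.493 × 0.507 + 0.743 × 0.257)]² / 0.25² = (1.3468 + 0.5588)² / 0.0625 = 58.1, that is 59 per arm.
- With continuity correction: (58.1/4) × [1 + √(1 + 4/(58.1 × 0.25))]² = 65.9, that is 66 per arm.

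The stated 66 is reproduced. It concerns a binary outcome, and the handling of counts does not alter it.

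**Assumptions for the counts (none is in the article).** Poisson counts around a log-normal rate, mean 30 per month, 30% reduction (ratio 0.7), 66 per arm. Between-woman log-SD *a* = 0.5, 0.7 or 1.0, with visit-to-visit log-SD *b* = 0.4, 0.5 or 0.5 respectively.

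**Why adjustment helps.** With equal variance V at both visits and correlation ρ, change has variance 2V(1 − ρ) and ANCOVA has residual variance V(1 − ρ²). Their ratio is (1 + ρ)/2, which is below 1 for any ρ below 1.

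**Hand check, mildest case (*a* = 0.5, *b* = 0.4).**

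- Variance, baseline or control follow-up: 30²(e^0.41 − 1) + 30 = 900 × 0.5068 + 30 = 486.1.
- Control covariance: 900(e^0.25 − 1) = 255.6.
- Intervention follow-up: variance 21² × 0.5068 + 21 = 244.5; covariance 0.7 × 255.6 = 178.9.
- Change: variances 2(486.1 − 255.6) = 461.0 and 486.1 + 244.5 − 357.8 = 372.8. SE = √(833.8/66) = 3.55. The mean difference is 0.3 × 30 = 9. Power ≈ Φ(9/3.55 − 1.96) = Φ(0.57) = 72%.
- ANCOVA on counts: pooled slope (255.6 + 178.9)/(2 × 486.1) = 0.447. Residual variances 486.1 − 228.5 + 97.1 = 354.7 and 244.5 − 159.9 + 97.1 = 181.7. SE = √(536.4/66) = 2.85. Power ≈ Φ(9/2.85 − 1.96) = Φ(1.20) = 88%.

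The simulated values are 73% and 89%. The normal approximation gets rougher as skew grows, so simulation is used throughout the table.

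**Simulated power, no zero months.**

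| Between-woman log-SD | ANOVA of change | ANCOVA, counts | ANCOVA, ranks | ANCOVA, log counts |
|---|---|---|---|---|
| 0.5 | 73% | 89% | 93% | 93% |
| 0.7 | 48% | 67% | 79% | 80% |
| 1.0 | 37% | 51% | 71% | 72% |

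Against ANOVA of change, ANCOVA on counts gains 16, 19 and 14 points; ANCOVA on ranks gains 20, 31 and 34.

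**Dependence on spread.** A second set of simulations used a mean of 60 per month, the same 30% reduction, and correlations of 0.5 or 0.7 on the log scale. There the log-SD is the total at a visit. Power of ANOVA of change ran from 100% at log-SD 0.3 down to 16% at log-SD 1.2 with correlation 0.5. At 0.3 every method was at or near 100%, so no loss could be seen. With no true effect, ANOVA of change rejected in 3.8% to 5.7% of runs.

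**Zero months.** The Participants section admits women who worked at some time in the preceding six months, so a month without clients is possible. Zeros were added independently at each visit (an assumption). In the mildest scenario, ANCOVA on log(count + 0.5) fell to 46% against 61% for ANOVA of change with 5% zeros, and to 34% against 52% with 10%. ANCOVA on counts and on ranks stayed above ANOVA of change in all nine combinations (three spreads by 0, 5 and 10% zeros), with type I error of about 3 to 6%. Negative binomial regression with robust errors and dispersion fixed at 0.5 reached 11 to 12% type I error in the most skewed scenario with zeros.

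**The case against.** The strongest reply is that the article never expressly sends these counts to the ANOVA. It calls them other information collected, attaches no hypothesis to them, and does not itemise the sexual health risks to be analysed. The abstract links ANOVA to the primary outcome and the psychological measures. How a skewed secondary variable is transformed is commonly left to an analysis plan, which is not shown here. This part stands: inclusion of the counts is a natural reading but not an explicit one, and the missing detail on transformation is no fault. What can be criticised is the choice that is stated, analysis of change, which is the only between-arm method given for sexual risk.

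A reader might infer that a real fall in partners or acts would probably be missed. The documents do not support that. They give no client volumes, no variance and no target effect on counts. The path they describe runs from psychological health to condom use, and they do not say that the programme aims at fewer partners. A proportional effect on log-normal counts also favours log-scale methods by construction.

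A reader might also take a log or negative binomial model as the obvious cure. The zero-month results show that neither is safe as a default. Finally, the arithmetic mean is a legitimate target, because high-volume women matter for exposure. ANCOVA on the counts keeps that target and still gains over change.

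**Conclusion.** The concern holds as a minor point about secondary, unpowered outcomes. If acts and partner counts are right-skewed and vary widely between women, ANOVA of change gives up about 14 to 19 points of power against ANCOVA on the same counts, and 20 to 34 points against ANCOVA on ranks. These figures rest on the assumed spread, mean, 30% proportional effect and absence of zero months. With mild spread no loss was visible, partly because every method was then near its ceiling. Validity is not in question: type I error is kept, and neither the condom-use outcome nor the 66 per arm changes. Whether ANOVA suits the binary condom-use outcome is a separate matter, not judged here.

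**What to change.** Under Data analyses, take the counts of acts and partners out of the change-score analysis. State that follow-up counts will be compared between arms with the baseline count as covariate, using either:

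- ANCOVA on ranks, with a separately reported effect estimate, since the rank test does not supply one; or
- ANCOVA on the counts, reporting the adjusted mean difference with its 95% CI.

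Allow ANCOVA on log counts only if zero months prove negligible in data pooled over arms, and then label the result a ratio of geometric means, not a ratio of means. Saying which variables make up the sexual health risks would also remove the ambiguity about scope.

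The cost is a few lines of wording. Baseline values are already collected, and no further data or participants are needed. The price is the extra effect estimate if ranks are chosen.

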## Background

HIV infection remains a global public health challenge. In low-to-middle income countries in Eastern Europe and Asia, there was a 25% increase in new infections between 2001–09 [1]. In order to reduce transmission and the spread of infections, targeted programmes at high-risk populations are essential [2]. Among various high-risk groups, female sex workers (FSWs), who are associated with a greater number of sexual partners compounded by high mobility, have been identified to play a significant role in the transmission of HIV and other sexually transmitted infections (STIs) [3]. This is due to the fact that FSW could potentially act as a “bridge” to spread the virus to their clients and families of their clients and so forth to the general public, and to the neighbouring regions and vice versa. According to the Global Health Sector Strategy on HIV/AID 2011–15 recently published by the World Health Organisation (WHO), identifying and optimising contextually-tailored HIV prevention programmes for high risks populations was strongly recommended [4].

Current HIV prevention strategies for FSWs include harm reduction, biomedical and structural interventions operating at individual and population levels. Systematic reviews on the effectiveness of these HIV prevention programmes indicated that harm reduction programmes based on the Health Belief Model [5], Theory of Reasoned Action [6], or Theory of Planned Behaviour [7] are commonly used and mainly involve promoting condom use by increasing associated knowledge, removing barriers for access, or changing their beliefs and attitudes. In addition, interventions targeted at FSWs are effective [8,9]. Nonetheless, these programmes seldom address the issues that initially bring these women into commercial sex and the associated psychological distress. It is thus argued that since many of these interventions do not take into consideration the emotion and personal circumstances of the target population, they are unlikely to have sustainable effects [10].

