#### Research aims and objectives

The Personal Resilience and Enrichment Programme (PREP) has been developed according to resilience framework for a trial with FSWs in Hong Kong. The aim of this study is to seek a new direction for HIV prevention by investigating the effectiveness of PREP in FSWs. Through promoting FSW psychological health, it is hypothesised FSWs will take better care of their physical well-being and actively practise HIV preventive measures, and hence reduce their HIV risks. Specifically, the objectives of this study include:

1. To evaluate the effectiveness of PREP, the resilience-promoting intervention, in enhancing FSWs’ overall resilience, reducing their psychological distress, and eventually reducing HIV risk behaviours among FSWs in Hong Kong.

2. To explore the mechanism of how individual resilience factors operate to promote better psychological outcomes and decreasing HIV infection among FSWs.

This study is a randomised controlled trial to test the hypothesis that the participants in intervention group, as compared to those in the control group receiving usual care, would have an improvement in HIV preventive behaviour through the increase in overall resilience and in terms of their self-efficacy, self-esteem and coping strategies. At the same time, it is hypothesised that this cohort of FSWs’ psychological distress would be reduced upon completion of the programme and such improvements would be continued at least in the 3-month post-intervention period. The study will further explore the operation of the resilience model by specifying the association of stress perceived by FSWs, and the effects of the resilience attributes (self-esteem, self-efficacy, and coping strategies) on their level of psychological health and HIV preventive behaviours (Figure 1).

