## Methods & design

### Study design

This is a randomised controlled trial in which participants will be randomly assigned to either intervention group or usual care as the control group. Participants in the intervention condition will receive the 6-session PREP, whereas participants in the control group will receive usual care. Outcome measures of all participants will be collected at baseline, completion of intervention or 6 to 12 weeks after baseline for control group, and 3 months thereafter.

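### The article names no between-arm comparison at 3 months for its persistence hypothesis, and a significant group-by-time ANOVA alone would not support that hypothesis

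*Protocol article*

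**What the plan says.** Under Research aims and objectives, the article hypothesises that "psychological distress would be reduced upon completion of the programme" and that "such improvements would be continued at least in the 3-month post-intervention period". This is a statement about the 3-month visit as well as the end of treatment.

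Study design sets three assessments: outcomes are "collected at baseline, completion of intervention or 6 to 12 weeks after baseline for control group, and 3 months thereafter".

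Data analyses states that change in the sexual-risk and psychological scores (self-esteem, self-efficacy, coping, resilience and GHQ) "over time between two groups will be analysed using analysis of variance with intention-to-treat analysis", at the 0.05 level. The Abstract agrees: outcomes "will be measured at baseline, post-treatment and 3-month post-intervention and differences assessed by ANOVA". Neither place says whether the test is the group-by-time interaction, the group main effect or a separate analysis of change at each visit. The correlations, regressions and structural equation model in the same section address association and mechanism, not whether the arms still differ at 3 months.

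**The concern.** The null hypothesis behind the persistence claim is that the arms do not differ at 3 months. An analysis of change over time between two groups, with three visits, is most naturally a group-by-time interaction. Its null hypothesis is that the two mean profiles are parallel over all visits. That null is false whenever the arms separate at any follow-up visit, including when they separate only at the end of treatment and have come together again by 3 months. A significant interaction would then be compatible both with the persistence hypothesis and with its negation. If it were the only evidence, the trial could not say which had occurred.

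**Working it through.** The article gives no effect size or between-visit correlation for the psychological scales, so these are assumed and varied.

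**Inputs**
- n = 66 per arm, two-sided alpha 0.05 (Sample size). The stated size reproduces: 49.3% against 74.3% with 80% power gives 59 per arm uncorrected and 66 with a continuity correction. It is used here only as n.
- Three visits (Study design).
- Assumed: normal scores with SD 1, complete data, benefit d = 0.3 to 0.5 SD, equal correlation ρ = 0.3 to 0.7 between visits.

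**Step 1: the interaction cannot separate the two patterns.** Its noncentrality depends on the between-arm differences centred over visits:

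λ = (n/2) × Σ(δ_j − δ̄)² / (1 − ρ), on 2 and 2 × (132 − 2) = 260 df.

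- Sustained (0, d, d): mean 2d/3, so the centred sum of squares is (4 + 1 + 1)d²/9 = 2d²/3.
- Vanished (0, d, 0): mean d/3, so it is (1 + 4 + 1)d²/9 = 2d²/3.

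The sums are identical, so power is identical for any d and n. At d = 0.5 and ρ = 0.5, λ = 33 × 0.1667 / 0.5 = 11.0, and power is 0.848 for both patterns. At ρ = 0.3, λ = 7.86 and power is 0.704 for both. At ρ = 0.7, λ = 18.3 and power is 0.975 for both. With d = 0.3 and ρ = 0.5, λ = 3.96 and power is 0.408 for both. With 53 per arm (about 20% loss), d = 0.5 and ρ = 0.5, it is 0.756 for both.

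**Step 2: unequal correlation.** Where correlation decays with the time between visits (AR(1), 0.7, d = 0.5), the Greenhouse-Geisser interaction test rejected in 0.91 of simulated trials if the benefit was sustained and 0.97 if it had vanished. Exact equality is lost, but the ambiguity is not.

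**Step 3: tests aimed at 3 months (d = 0.5, ρ = 0.5).**
- Unadjusted change from baseline: SE = √(2(1 − ρ) × 2/n) = √(2/66) = 0.174. Then 0.5/0.174 = 2.87, and power ≈ Φ(2.87 − 1.96) ≈ 0.82.
- Baseline-adjusted difference: SE = √((1 − ρ²) × 2/n) = √(0.75 × 2/66) = 0.151. Then 0.5/0.151 = 3.32, and power ≈ Φ(3.32 − 1.96) ≈ 0.91. The same formula gives about 0.85 at ρ = 0.3 and 0.98 at ρ = 0.7.

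**Side by side (d = 0.5, ρ = 0.5, 66 per arm)**

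| Test | Benefit sustained | Benefit gone by 3 months |
|---|---|---|
| Group-by-time interaction | 85% | 85% |
| Group main effect over three visits | 65% | 22% |
| Change at 3 months, unadjusted | 82% | 5% |
| Difference at 3 months, baseline-adjusted | 91% | about 5% |

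The main-effect row and the vanished-benefit figures for the two 3-month tests come from simulation; in the adjusted test the latter ranged from 4.4% to 5.6% over the scenarios run.

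**The case against.** The strongest reply is that the article never names the interaction. An ANOVA of change scores could be run separately at each follow-up visit. That would include a direct 3-month test, which rejects only about 5% of the time when the benefit has vanished. This stands: the equal-rejection result is conditional on the interaction reading and cannot be attributed to the plan without that condition. The main-effect reading is less of a rescue, since it still rejects 22% of the time for a vanished benefit.

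Three stronger inferences might tempt a reader, and the document does not support them.
- That persistence is tested only by this ANOVA. This is a condensed article and no full protocol or analysis plan is shown; visit contrasts may be specified there. One can say only that the article names no other between-arm analysis.
- That a short-lived effect will be reported as lasting. No such decision rule is stated, and with outcomes collected at every visit, a lost benefit would show in the 3-month means.
- That lasting psychological gain is what sets the programme apart. The Background comment that "they are unlikely to have sustainable effects" concerns existing HIV-prevention interventions, and the article itself credits earlier resilience studies with long-term psychological improvement.

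The hypothesis refers most directly to distress; extending it to the resilience measures is a reasonable reading but not an explicit one. On power, the gain of the adjusted contrast over the interaction (91% against 85%) should not be credited wholly to targeting 3 months: the unadjusted 3-month test has 82%, so part of the gain comes from baseline adjustment.

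**Conclusion.** The point holds in a limited form. The article states a hypothesis about the 3-month visit and does not tie it to a between-arm contrast at that visit. If the named ANOVA is the group-by-time interaction, a significant result alone would not support persistence, because it is equally likely whether the benefit is sustained or lost: about 85% each at 0.5 SD and correlation 0.5, 70% to 98% over correlations 0.3 to 0.7, and 41% each at 0.3 SD and correlation 0.5. The equality is exact under equal correlations. The percentages rest on assumed effect sizes and correlations and on complete data. The matter concerns the psychological outcomes, which are secondary, and it calls for a clearer and better-targeted analysis statement; it does not show that a misleading conclusion is planned.

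**What to change.** State in Data analyses that the persistence hypothesis is tested by the between-arm difference at the 3-month visit, adjusted for the baseline score and reported with a 95% CI for each psychological outcome. A model of both follow-up visits with an arm-by-visit term would supply it. Report the post-treatment difference separately, and say that persistence will not be inferred from an overall group-by-time F test.

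The cost is a few sentences. The data are already to be collected, and no participants are added. The small downside is that a transient effect could no longer be used to support the durability claim.
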